## Methods

### Design

This double-blind, randomised, sham-controlled trial will compare rTMS and tDCS acceptability and clinical outcomes in patients with AN. This study protocol was prepared in accordance with the SPIRIT and CONSORT guidelines. Participants will be randomised to one of four groups (2:1:2:1 ratio): active or sham tDCS, or active or sham rTMS. The brain stimulation protocols involve 84 sessions of tDCS (active or sham) or 56 sessions of rTMS (active or sham) over an 8 week treatment period. Participants in all groups will also receive treatment as usual (TAU) across the study duration. Following the end of 8 week randomised controlled period assessment, participants in all groups will have the option of receiving an additional open label 12 weeks of at-home, remotely supervised tDCS. A follow up assessment will be conducted at 20 weeks post treatment. A flowchart of the study is shown in Fig. 1.

**Fig. 1 Fig1:**
[figure not shown]
Schematic diagram of TRENA study procedures

### Eligibility criteria

Male and females will be eligible for enrolment if they meet the following criteria: (1) are aged 16 years or over, (2) have a current Diagnostic and Statistical Manual of Mental Disorders (5th edition DSM-5) diagnosis of anorexia nervosa, (3) are willing and able to participate and comply with study requirements, and (4) worked or studied in a context requiring some proficiency in spoken English (to ensure validity of neuropsychological testing). To ensure patient safety during the study, all participants must be under ongoing care by his/her treating psychiatrist. Potential participants will be excluded in the case that one or more of the following criteria are present: (1) inability to provide informed consent, (2) contraindications to tDCS/rTMS (i.e., metal or devices in head which could interfere with stimulation effects or cause heating, and medical conditions which could increase risk of adverse side effects, e.g., seizures, tinnitus; [44], (3) failed to respond to an adequate course or rTMS (4 weeks) within the current illness course, (4) had ECT in the last 3 months, (5) Montreal Cognitive Assessment (MoCA, Nasreddine, et al. [65]) score of < 26, (6) risk of significant self-harm or suicide as assessed by the study psychiatrist(s), (7) currently enrolled in another interventional clinical trial or using an investigational device/product.

### Recruitment and setting

Participants will be recruited from inpatients in the Eating Disorder Programme for the treatment of anorexia nervosa at Ramsay Northside Clinic, St Leonards, Sydney. The study will recruit 70 participants over a two-year period.

### Interventions

#### Repetitive transcranial magnetic stimulation (rTMS)

rTMS will be administered using a MagPro TMS device. rTMS involves the application of transient magnetic pulses which induce small currents in the underlying cortex via the principal of electromagnetic induction. Both sham and active rTMS will be commenced while participants are inpatients and will continue over the 8 weeks of acute treatment. rTMS will be twice per weekday (separated by ≥ 2 h) [53] over the first 4 weeks (Monday-Friday) and then twice daily per day (separated by ≥ 2 h), given on 2 days each week for the following 4 weeks. Treatment every weekday for 4 weeks is consistent with a typical therapeutic course for intermittent theta-burst stimulation (iTBS) [9]. A taper period over the following 4 weeks is consistent with clinical recommendations for rTMS [59] and has been designed to coincide with participants attending the hospital for day patient programs, 2 days per week, or continuing in outpatient care following discharge from the inpatient program. Active rTMS will be administered using a patterned frequency stimulus called intermittent theta-burst stimulation (iTBS) [40]. This form of rTMS was chosen because a recent large multicentre trial showed 3 min of iTBS attained the same therapeutic effect as 30 min of standard rTMS, leading to FDA approval for depression [9]. Each rTMS treatment session will comprise an extended iTBS session, i.e., 6.6 min, delivered at 100% resting motor threshold (RMT). Extended iTBS has previously been found safe and effective in patients with depression [15]. It will be targeted to the left DLPFC (based on F3 using the 10-20 International EEG system), consistent with the prior RCT of rTMS for AN [20, 21]. For sham rTMS, a sham coil will be placed on the head with no active stimulation administered.

#### Transcranial direct current stimulation (tDCS)

tDCS will be self-administered using the 1 × 1 tDCS mini-CT Stimulator (Soterix, USA: ARTG: 284637) with two saline-soaked sponge electrodes held in place on the scalp using the Soterix Ole-2 headband [72]. The device is intended to treat different neurological and psychiatric disorders. tDCS involves the passing of weak electrical current through the brain via electrodes placed upon the scalp. The current modulates the resting membrane potential of stimulated neurons which causes changes in neuronal excitability. The anode will be placed over the left F3 (10-20 System) and the cathode over F4 (electrode sizes 5 × 5 cm, 25 cm^2^) using the BEAM F3 method [61]. This montage was chosen to target the left DLPFC, consistent with prior studies of tDCS in AN [7, 45, 71]. Sham and active tDCS will be given 84 sessions over 8 weeks of TAU: twice daily (separated by ≥ 2 h) over the first 4 weeks, and daily over the second 4 weeks of the 8 week treatment period. Twice daily tDCS was found safe and effective in previous pilot trial in AN [71]. Active tDCS will be given continuously for 30 min at 2 mA. Sham tDCS will involve an initial ramping up to 1.0 mA and then a ramp down to 0 mA, with a similar ramp up and down at the end of the treatment. Participants receiving active or sham tDCS will self-administer treatment after receiving training, practice and credentialling consistent with our home-based tDCS protocol [3]. The research team will routinely monitor participant’s adherence to the intervention protocol and side effects from each treatment recorded on the Soterix Medical ElectraRx platform. The Soterix Medical ElectraRx solution is a software portal connecting stimulation administrators/clinicians and individuals with the data collected from Soterix Medical neuromodulation technologies including tDCS. At all times, the research team will have real-time access to the information collected by the individual’s device. They will also have access to the individual’s historical data, side effects, stimulation compliance, and warning signs.

### Optional open label active tDCS treatment

Following the end of 8 week randomised controlled period assessment, participants in all groups will have the option of receiving an additional 12 weeks of daily (1 session per day), at-home, remotely supervised active tDCS, until end week 20.

### Screening and enrolment

A study psychiatrist will discuss participation in detail before obtaining written informed consent. Potential participants will be assessed and screened for eligibility before enrolment to the study. Participants’ treating psychiatrist will provide their clinical characteristics including a Diagnostic and Statistical Manual of Mental Disorders, (5th edition, DSM-5) diagnosis, duration of illness and information about medication. Participants will complete the Montreal Cognitive Assessment (MoCa; Nasreddine, et al. [65]) and TMS Adult Safety Screen [44].

### Allocation

Once eligibility criteria are met and informed consent obtained, participants will be randomly allocated to one of four treatment arms: active rTMS or sham rTMS (2:1 ratio) or active tDCS or sham tDCS (2:1 ratio). The R package randomizeR will be used to generate the sequences, based on Efron’s biased-coin design. Generation of the sequences will be carried out by the study statistician. Central randomisation will be implemented using the Research Electronic Data Capture (REDCap) Randomisation Module and the study coordinator will be responsible for assigning each participant to a treatment group prior to commencing research treatment. The randomisation sequence as generated will be imported into REDCap and will consist of a code (e.g. ‘A’, ‘B’, ‘C’ or ‘D’ indicating a treatment arm).

### Outcome measures

Outcome measures and administration timepoints are presented in Table 1.

**Table 1 Tab1:** Outcome measures of the RCT

Measure	Mode	Baseline	Weeks 1–3	Week 4	Week 8	Weeks 10, 12, 14, 16, 18	Week 20
Core an symptoms							
Eating Disorder Examination Questionnaire, EDE-Q, *total score, subscales scores* [30]	Electronic	✓		✓	✓	✓	✓
**Weight—**BMI, *kg/m*^*2*^		✓		✓	✓		✓
Mood							
Montgomery Asberg Depression Rating Score, MADRS, *total score* [64]	Electronic	✓	✓	✓	✓		✓
Neurocognition							
**Perseveration** Wisconsin Card Sorting Test, WSCT, *numbers of errors* [33]	Computer	✓			✓		✓
**Response inhibition** STROOP Colour Word Test, *response time in milliseconds* [70]	Computer	✓			✓		✓
**Field dependence vs independence** Group Embedded Figures Test, GEFT, *completion time in seconds, total number of correct forms* [75]	Paper	✓			✓		✓
**Attention and cognitive flexibility** Trail Making Test parts A & B, TMT, *completion time in seconds* [66]	Paper	✓			✓		✓
Psychological symptoms							
Depression Anxiety and Stress Scale, DASS-21, *subscales total scores* [54]	Electronic	✓	✓	✓	+ Weeks 5–7✓	✓	✓
Quality of life							
The Assessment of Quality of Life Instrument, AQoL-4D, *total score* [38]	Electronic	✓			✓		✓
Interpersonal relations							
Circumplex Scales of Interpersonal Efficacy, CSIE-32, *subscales total scores* [52]	Electronic	✓			✓		✓
**Experience of treatment** OPTIONAL Semi-structured interview	Zoom				✓		✓
**Assessment of blinding**	Electronic				✓		
Economic outcomes							
Administration cost	Hospital data		✓	✓	✓	✓	✓
Medications			✓		✓		✓
Psychology sessions							✓
Length of stay				✓	✓		
Readmissions							✓

#### Primary outcomes

The efficacy and acceptability of rTMS and tDCS treatments will be this trial’s primary outcomes. The efficacy will be measured by a mean improvement of the Eating Disorder Examination Questionnaire (EDE-Q; Fairburn [30]) from baseline to end of treatment at 8 weeks. The EDE-Q is widely considered the gold standard tool for assessment of eating disorder (ED) psychopathology [1]. It is a self-report measure and includes four sub-scales related to the cognitive features of eating disorders: Restraint, Eating Concern, Shape Concern and Weight Concern. This measure for assessing change in the severity of eating disorder psychopathology was chosen due to its sensitivity in recognising behavioural and cognitive change in the recovery for AN [18]. Number of completed sessions for active tDCS and active rTMS in the acute 8-week RCT period will indicate acceptability of both treatments.

#### Secondary outcomes

A range of secondary outcome measures will be administered to further determine rTMS and tDCS treatment effects on: (1) weight, (2) mood, (3) neurocognition (attention and cognitive flexibility, field dependence vs independence, response inhibition, perseveration), (4) psychological symptoms, (5) quality of life, (6) interpersonal relations, (7) experience of treatment (optional semi-structured interviews), (8) economic outcomes (health sector costs including rTMS and tDCS administration, medications, psychology sessions, length of stay, and number of hospital readmissions). See Table 1 for measures.

### Optional interview

Between weeks six and eight, semi-structured qualitative interviews will be offered to all participants to share their views on the experience, and perceived barriers and facilitators for treatment change with rTMS and tDCS. Participants who agree to participate will be interviewed on a one-to-one basis via videoconferencing, following a semi-structured guide (adapted version of topic guide developed by Dalton et al. [19]). All interviews will be audio recorded and will last 10–20 min. Participants will be blinded to the treatment allocation for the first interview (between weeks 6–8 of treatment) and they will be unblinded for the second interview (at week 20 follow up) when they will have an opportunity to share their experience of at home self-administered tDCS.

### Blinding

In this double-blind trial, participants, their treating psychiatrist, ward staff, and a study staff member (who will conduct blinded assessments of mood secondary outcome measures) will be blinded after assignment to an initial intervention until the database is locked and the primary analysis completed. The integrity of blinding will be evaluated at the end of randomised treatment assessment (at 8 weeks follow up) by asking participants and the mood rater conducting the secondary mood outcome rating to indicate which treatment group they thought the participant was allocated to (active tDCS, sham tDCS, active rTMS or sham rTMS) and their confidence (rated 0% = not confident to 100% confident).

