#### Secondary outcomes

Analyses of secondary outcomes will be competed in the mITT population. The size of the treatment effect will be the difference in outcome data (BMI, questionnaires, neurocognitive outcomes) between the active and sham treatment arms for both tDCS and rTMS, respectively, at 4 weeks, 8 weeks, and 20 weeks post treatment. These effect sizes will control for pre-treatment scores. Descriptive statistics will be used to show remission rates for all treatment arms at post 8 weeks and 20 weeks post treatment. Generalised linear mixed models will be used to compare the treatment arms for mood and psychological symptom outcomes. Exploratory analyses will investigate associations between changes in mood and neurocognition with active tDCS and rTMS, and improvement in core eating disorder symptoms.

Generalised linear models will be used to compare cost and quality of life/utility values (from AQoL-4D) between treatments arms over the 8 week randomised treatment. Cost effectiveness analysis will compare the health outcomes and economic outcomes (costs of duration of inpatient stay and readmissions during the follow up period) associated with both treatment modalities.

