#### Qualitative data

Since thematic saturation may be achieved in 12 interviews [36], our aim is to collect qualitative data for 10–20 participants from each treatment group. Audio-recorded interviews will be transcribed verbatim in accordance with standardised guidelines [60] and will be analysed using inductive approach qualitative methods with use of the framework of thematic analysis [11]. This will include coding and generation of themes from participants accounts of their experience of rTMS and tDCS treatment.

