### Trial status

Clinical Trial Protocol version 8 dated 11 July 2023. Recruitment commenced in August 2023 and will end in May 2025.

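### Participants are to stay blinded until database lock, yet those who take the optional second interview are unblinded at their own week 20, when secondary outcomes are still due

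*Protocol article*

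**What the plan says.** The Blinding section names participants, their treating psychiatrist, ward staff and the staff member who rates mood, and says that they "will be blinded after assignment to an initial intervention until the database is locked and the primary analysis completed". The success of blinding is checked once, at week 8.

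The Optional interview section sets a different end to the participants' blind. "Participants will be blinded to the treatment allocation for the first interview (between weeks 6–8 of treatment"), whereas "they will be unblinded for the second interview (at week 20 follow up"). The interview is voluntary but open to everyone: "semi-structured qualitative interviews will be offered to all participants". Under Qualitative data the target is given as "our aim is to collect qualitative data for 10–20 participants from each treatment group".

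Table 1 places the EDE-Q, DASS-21, AQoL-4D, CSIE-32, MADRS, BMI and the cognitive tests at week 20, the same time point as the second interview. The Secondary outcomes part of the Analysis section plans to estimate differences "between the active and sham treatment arms for both tDCS and rTMS, respectively, at 4 weeks, 8 weeks, and 20 weeks post treatment". On timing, Trial status states: "Recruitment commenced in August 2023 and will end in May 2025". Recruitment and setting describes one clinic.

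**The concern.** Week 20 is a date on each participant's own calendar, whereas database lock is a single event for the whole trial. Nothing in the article ties the second interview to the lock. With rolling recruitment, an early participant is told the allocation long before the lock, while the blinding statement says that this does not happen. Staff cannot follow both rules, and a trial report that repeated the blinding statement would be untrue for the participants interviewed at week 20.

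What is at stake is mainly the set of week-20 comparisons of active with sham. Most of the questionnaires due then are answered by the participant. The article says of the EDE-Q: "It is a self-report measure and includes four sub-scales related to the cognitive features of eating disorders". The MADRS rater stays blinded under the Blinding section, but a participant who knows the allocation may answer differently or mention it. Nothing stated places these assessments before disclosure, and the one check of blinding at week 8 would not detect a later loss. Disclosure cannot be undone at the analysis stage.

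**Working it through.** **Do the two rules have the same object?** The interview section contrasts being unblinded at the second interview with being blinded to treatment allocation at the first. The natural object of the unblinding is therefore the randomised allocation. The extension phase is described as open label and active, so there is nothing about it to unblind.

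**Could the lock come first?** The plan gives no lock date, so this is a calendar check.

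Inputs: recruitment starts between 1 and 31 August 2023 and ends between 1 and 31 May 2025 (Trial status); 70 participants (Recruitment and setting); primary efficacy time point week 8 (Outcome measures, Primary outcomes). Assumptions: uniform accrual and no dropout.

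- First week-20 visit = start + 140 days: 19 December 2023 to 18 January 2024. That is 67 to 76 weeks before recruitment ends.
- Earliest complete week-8 data = end + 56 days: 26 June to 26 July 2025.
- Earliest complete week-20 data = end + 140 days: 18 September to 18 October 2025.

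Let R be the length of recruitment in days. Over the four combinations of first and last days of the stated months, R is 609, 639 (twice) or 669.

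- Share reaching week 20 before a lock of week-8 data alone is possible = (R + 56 − 140)/R = 1 − 84/R. This gives 0.862, 0.869 and 0.874, or 60.3 to 61.2 of 70.
- Share reaching week 20 while the site is still recruiting = 1 − 140/R. This gives 0.770, 0.781 and 0.791, or 53.9 to 55.4 of 70.

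If the lock also covers week-20 data, nearly every second interview precedes it.

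**Sensitivity to the meaning of week 20.** The Design section puts the follow-up 20 weeks post treatment. If that meant week 28, the first disclosure would be start + 196 days, from 13 February to 14 March 2024, still more than a year before recruitment ends. The share reaching it before a week-8-only lock would be 1 − (196 − 56)/R = 1 − 140/R, or 77–79%. The conflict remains.

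**How many are affected?** These shares describe who reaches the visit, not who is interviewed. If the target of 10–20 per treatment group refers to the two modalities, it means 20 to 40 of 70. If it refers to the four arms, it means at least 40. The article does not say how many of these are expected at the second interview.

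**The case against.** The best case on the other side concedes the conflict of wording and disputes its consequences. Most of it stands.

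- **Scope.** A reader might infer that every participant is unblinded at week 20. The text supports this only for those who take an optional interview, and the number depends on uptake.
- **Primary outcome.** A reader might infer that the week-8 result is compromised. Each participant's own week-8 EDE-Q precedes disclosure. Allocation is individual, so learning one person's arm does not reveal another's. The Analysis section defines the primary effect as change from before to after treatment within the active arms. What remains is an indirect route, by disclosure to clinicians or other participants at the single site. It is possible but not shown: the extension is at home and interviews are by videoconference.
- **Week-20 outcomes.** These are secondary, and optional open-label active tDCS in all groups already means that they are not a clean randomised contrast. The mood rater is not unblinded. The order of questionnaires and interview may be settled in the full protocol, so bias is an unprotected risk and not a certainty.

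Two replies do not succeed. Reading the unblinding as referring only to the open-label tDCS goes against the sentence's own contrast with treatment allocation. An early lock of week-8 data comes too late for most participants, as the dates show.

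**Conclusion.** The plan is wrong as written: the two sections give incompatible end points for the participants' blind. Under uniform accrual and no dropout, about 86–87% of participants reach week 20 before even a week-8-only lock could take place, so the conflict applies to most of those interviewed.

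The consequence is limited. The secondary week-20 active-versus-sham comparisons lack stated protection from prior disclosure: EDE-Q, DASS-21, AQoL-4D and CSIE-32 directly, and MADRS through participants' answers. The size of any bias cannot be derived from the article, since it depends on uptake and on the order of events at the visit. The documents do not support a conclusion that the primary outcome is biased, or that all 70 participants are unblinded early.

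**What to change.** Reconcile the Optional interview and Blinding sections in one of two ways.

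1. Hold the week-20 interview without revealing the randomised allocation, and disclose it after database lock and the primary analysis. Participants can still describe their experience of at-home tDCS, which they know to be active. The Blinding section then stands, and the sentence on unblinding is removed.
2. Keep disclosure at week 20, but require that all week-20 outcome assessments, including MADRS, are complete beforehand. Ask participants not to share their allocation with the mood rater, treating staff or other participants. Amend the Blinding section to say that interviewed participants are blinded only until their week-20 assessments are complete.

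The first option keeps the stated safeguard whole but excludes any interview question that depends on knowing the allocation. The second keeps such questions but relies on participants' discretion. The cost is wording plus either later disclosure to participants or a fixed order at the visit. Neither option changes the sample size or the analysis.

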### Adverse event monitoring

Participants in all treatment arms will complete a side effects questionnaire after every treatment session, the rTMS group via RedCap survey and tDCS group directly via ElectraRx. Trained staff who administer all rTMS sessions will also record adherence to the intervention protocol. Participants’ adherence to tDCS will be monitored by the tDCS device which records of the number of treatments administered. The research team will routinely monitor participant’s adherence to the intervention protocol and side effects from each treatment.

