### Ethical considerations

Reasonable precautions against harms and steps to mitigate risks will be taken. To minimise the potential risk for adverse effects, participants will be screened for potential contraindications for both tDCS and rTMS treatment prior to providing informed consent. Safety and adverse effects will be closely monitored by study staff over the course of the trial and through ongoing care by the participants’ treating psychiatrist, who will continue to oversee clinical progress and the welfare of his/her patient over the course of the study. Every 6 months reports of any serious adverse events will be monitored by an independent medical monitor.

To ensure confidentiality, all data collected will be de-identified. Where participant consent is provided for data to be re-used and shared with other researchers for future research projects, data will only be provided in a de-identified format and with separate ethics approval. No identifiable information will be reported in any format, thus protecting the confidentiality of participants and other information collected during the study.

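### The only structured side-effect questionnaire described is tied to treatment sessions, so it ends when sessions end and gives tDCS 84 collection points against 56 for rTMS

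*Protocol article*

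**What the plan says.** Under Adverse event monitoring, the Protocol article fixes the trigger for side-effect collection: "Participants in all treatment arms will complete a side effects questionnaire after every treatment session". The platform differs by modality, "the rTMS group via RedCap survey and tDCS group directly via ElectraRx", and the research team's routine review is likewise of "side effects from each treatment".

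The Design section sets the volume: "84 sessions of tDCS (active or sham) or 56 sessions of rTMS (active or sham) over an 8 week treatment period". After week 8, under Optional open label active tDCS treatment, "participants in all groups will have the option of receiving an additional 12 weeks of daily (1 session per day), at-home".

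Ethical considerations adds monitoring that does not depend on sessions. "Safety and adverse effects will be closely monitored by study staff over the course of the trial and through ongoing care" by the treating psychiatrist, whose care Eligibility criteria makes a condition of entry. For serious events: "Every 6 months reports of any serious adverse events will be monitored by an independent medical monitor".

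Table 1 schedules the outcome measures by calendar week and has no adverse event row. It does list the DASS-21, completed electronically, at baseline, weekly through weeks 1 to 8, at weeks 10, 12, 14, 16 and 18, and at week 20.

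**The concern.** A questionnaire triggered by a session collects data only from people who are having sessions. This has three consequences.

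- **Stopping treatment.** A participant who stops, possibly because of a side effect, triggers no further questionnaires. Whether the effect persisted, and whether anything new followed, is not recorded in structured form.
- **Different intensity by modality.** Both modalities are observed for 8 weeks, but tDCS participants are asked one and a half times as often. A per-participant summary, such as the proportion with any side effect, rises with the number of times the question is put.
- **After week 8.** Those who take open-label tDCS continue to be asked. Those who decline have no structured side-effect assessment described for weeks 9 to 20.

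The trial sets out to compare the acceptability of tDCS and rTMS and to inform a larger trial. Its acceptability outcome is the number of completed active sessions. Side effects are an obvious candidate explanation for a low count, yet the structured record of them stops when the count stops.

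**Working it through.** **Inputs.** Session schedules are from the rTMS and tDCS subsections of Interventions; totals are from Design; the open-label schedule is from its own section; the DASS-21 schedule is from Table 1. The article gives no side-effect rate, so the per-questionnaire probabilities in step 5 are assumptions.

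**1. Reproducing the article's session totals.**

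- tDCS, twice daily for 4 weeks then daily for 4 weeks: 2 × 7 × 4 + 1 × 7 × 4 = 56 + 28 = 84.
- rTMS, twice per weekday for 4 weeks then twice a day on 2 days a week for 4 weeks: 2 × 5 × 4 + 2 × 2 × 4 = 40 + 16 = 56.

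Both agree with Design. With one questionnaire per session, these are also the planned numbers of questionnaires, in the ratio 84/56 = 1.5.

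**2. Days with at least one questionnaire.** tDCS: 7 × 8 = 56. rTMS: 5 × 4 + 2 × 4 = 28. The ratio is 2.0. In weeks 5 to 8 alone it is 28 days against 8.

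**3. What is lost when a participant stops sessions.**

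| Stops after | tDCS collected / not triggered | rTMS collected / not triggered |
|---|---|---|
| week 2 | 28 / 56 | 20 / 36 |
| week 4 | 56 / 28 | 40 / 16 |
| week 6 | 70 / 14 | 48 / 8 |

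**4. After week 8.** Open-label tDCS is 12 × 7 = 84 sessions. If the session rule applies there too, a participant who takes it up has as many as 84 further questionnaires. One who declines has none described for 12 of the 20 weeks.

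**5. Effect of unequal frequency on a per-participant summary.** Suppose each questionnaire has the same chance p of carrying a report, independently and equally in both modalities. Then P(at least one report) = 1 − (1 − p)^n, with n = 84 or 56.

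| Assumed p | tDCS (n = 84) | rTMS (n = 56) | Gap in points |
|---|---|---|---|
| 0.5% | 34.4% | 24.5% | 9.9 |
| 1% | 57.0% | 43.0% | 14.0 |
| 2% | 81.7% | 67.7% | 13.9 |
| 5% | 98.7% | 94.3% | 4.3 |

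The gap has a ceiling. Writing x = (1 − p)^28, it equals x² − x³, which is largest at x = 2/3, where it is 4/27 = 14.8 points (p about 1.4%). The 1% and 2% rows are therefore close to the worst case. By construction the true difference is zero in every row.

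**6. Common time points already in place.** The DASS-21 is scheduled 8 + 5 + 1 = 14 times after baseline, on dates that depend on neither sessions nor modality.

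**The case against.** The strongest reply is that the article does not confine safety collection to sessions. Staff and the treating psychiatrist monitor participants throughout, and serious events go to an independent monitor. A reader might infer from the questionnaire rule that all adverse event collection stops when a participant stops treatment. The documents do not support that. What remains is narrower: the general statement names no instrument, time point or record from which arms could be compared, and the six-monthly review covers serious events only.

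Second, this is a journal article condensing protocol version 8, which is not shown. Reporting periods and follow-up after discontinuation are commonly left to the full document, and Table 1 is a table of outcome measures, so its lack of a safety row proves little. This stands. It cannot be said that people who leave treatment or decline open-label tDCS are never asked about side effects. The point rests on the rule the article states, not on what it leaves out.

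Third, a reader might infer that the modalities are observed over unequal periods. In the randomised phase they are not: both run for 8 weeks, and only the frequency differs. After week 8 the option is the same for all groups, so differences follow uptake. Each active arm also shares schedule and platform with its sham, so planned collection is balanced for the sham-controlled contrast. Only differential discontinuation would disturb it.

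Fourth, no comparative analysis of side effects is stated. Acceptability is a descriptive count of completed active sessions, and someone who stops because of harm lowers that count, so the loss is visible there. Reporting per session would remove the 84-versus-56 problem without changing collection. That is right as far as it goes, but a rate per session still describes only those attending.

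Finally, it is tempting to conclude that the arm losing most participants to side effects would show the fewest. This does not follow. The effect that prompts stopping may be recorded after the session that caused it. The questionnaire misses later and between-session events, and the net direction is unknown.

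**Conclusion.** The point holds in limited form, as a cheap improvement rather than a fault in the primary analysis. The only structured side-effect instrument the article describes depends on attendance. It ends with treatment, and over equal 8-week windows it gives 84 against 56 collection points, or 56 against 28 days.

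The counts follow directly from the stated schedules. The 4 to 14 point gaps for assumed rates of 0.5% to 5% are illustrations. They require a per-participant summary of any side effect, which the article does not propose, and equal, independent reporting at each questionnaire. Reports from one person are likely to be correlated, which would make the gap smaller. The size of any effect from discontinuation cannot be estimated, because the article gives no dropout figures.

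**What to change.** Keep the session questionnaire and report it as a rate per session. Add a short adverse event item set, covering new or worsening events since the last contact and the reason for any stop, to the electronic DASS-21 assessments at weeks 1 to 8, 10, 12, 14, 16, 18 and 20. State that it is completed whether or not sessions are attended and whether or not open-label tDCS is taken. Use this record for per-participant incidence by arm.

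The cost is a few items in an existing survey, with no new visit; the downside is slightly more participant burden. If the full protocol already provides calendar-based collection of this kind, one sentence saying so, and naming it as the source for between-arm summaries, is enough. For participants already enrolled, the added items would cover only the remaining time points, and the report should say so.
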